#### Data Analytical Plan

##### Phase 1

Qualitative data (ie, health information–seeking behaviors, determinants of trust, and opinions regarding chatbot development) will be transcribed and loaded into the qualitative analysis software ATLAS.ti (ATLAS.ti Scientific Software Development GmbH) for analysis. A hybrid deductive-inductive approach will be used, including initial code development based on prior literature and relevant conceptual models, which will be refined through iterative review of transcripts [28]. Data that do not fit the initial coding structure will be coded inductively; discussed by the analytic team; and incorporated as new codes, subthemes, or themes as appropriate. Analysis will explore variation by race and ethnicity and geographic location, with particular attention to rural-specific factors absent from urban-centric prior literature [17,18,22].

##### Phase 2

Across both sessions, data will include facilitator notes, audio-recorded and transcribed group discussions, and design artifacts generated during structured activities (information ecosystem maps and implementation insights). Transcripts and notes will be analyzed using rapid analysis with structured summary templates [29] to enable timely synthesis between sessions and inform iterative SARHAchat refinement. Summaries will be charted into comparison matrices to identify areas of convergence (validation) and divergence (further adaptation needs) across sessions 1 and 2. Each design modification will be recorded in a decision log that links participant feedback to the specific trust and acceptability determinants from phase 1 or to newly emerged determinants from sessions, producing a trust-by-design mapping and an analytical audit trail. Credibility will be supported via member checking as returning session 2 participants will validate whether session 1 concerns were addressed [30].

##### Phase 3

*Quantitative* data include demographic and socioeconomic characteristics; baseline digital health literacy (eHealth Literacy Scale) [31]; and implementation, usability, acceptability, appropriateness, and trust outcomes (Bot Usability Scale [32], Acceptability of Intervention Measure [33], Intervention Appropriateness Measure [33], and Trust Between People and Automation scale [34]) supplemented by back-end engagement analytics. Additionally, the Decision Self-Efficacy Scale (DSES) [35] will be measured at T0 and T1, and an adapted General Help Seeking Questionnaire (GHSQ) [36] will be administered at T1 to assess exploratory effectiveness signals. Due to the pilot sample size (n=75), we will perform descriptive analyses to present participants’ characteristics (eg, demographics, digital health literacy, and geographic location) and user experiences (eg, acceptability, usability, appropriateness, and trust). We will observe potential similarities and differences in implementation and use outcomes across participant characteristics (eg, race and ethnicity and geographic location), which we will interpret as hypothesis generating given the sample size. Usability data gathered by the SARHAchat dashboard will describe user activities such as session timing, completion and retention rates, and number of conversational exchanges. Feasibility outcomes will be organized within the RE-AIM framework against prespecified progression thresholds (Table 1). Consistent with the pilot’s feasibility scope, effectiveness through the DSES and GHSQ will be evaluated as exploratory and not a test of efficacy. We will report the mean within-person change in DSES and mean GHSQ. From the pilot sample, 20 participants will be purposively selected for semistructured interviews using maximum variation in engagement level, feasibility outcomes (including threshold missing cases), race and ethnicity, and geographic location to explain the range of quantitative findings. *Qualitative* data (ie, opinions and experiences regarding SARHAchat usability, acceptability, and trust) will be transcribed and analyzed using rapid thematic analysis with structured summary templates [28] and charted into a RE-AIM–aligned matrix [23,37,38]. A hybrid deductive-inductive codebook [28] will use RE-AIM domains as the deductive scaffold, with inductive codes capturing emergent themes. Integration of quantitative and qualitative data will be achieved through a RE-AIM–organized joint display [37,38] pairing each domain’s quantitative result with its qualitative explanatory theme to produce actionable meta-inferences (Multimedia Appendix 1). These meta-inferences will directly inform the progression decision, distinguishing modifiable design-level barriers from structural ones and guiding whether tool refinement or revision of the implementation strategy is needed [39].

**Table 1. T1:** Proposed feasibility outcomes, instruments, time points, and prespecified progression thresholds for aim 2, organized within the reach, effectiveness, adoption, implementation, and maintenance (RE-AIM) framework.

RE-AIM domain	Outcome and measure	Time point	Prespecified threshold
Reach	Enrollment rate and consent rate	16-wk recruitment window	≥60% of target (n≥45 enrolled)
Effectiveness	DSES^a^ [35] and adapted GHSQ^b^ [36]	DSES: T0^c^ and T1^d^; GHSQ: T1	Exploratory; no progression threshold; mean T0-T1 DSES change and T1 GHSQ
Adoption or engagement	Proportion completing the chatbot pathway among all enrolled	After interaction	70% or more of the participants completing a session
Implementation—usability	BUS-11^e^ [32]	T1	Mean BUS-11>4
Implementation—acceptability	AIM^f^ [33]	T1	Mean AIM>4
Implementation—appropriateness and trust	IAM^g^ [33] and TPA^h^ [34]	T1	Mean IAM>3; mean distrust<4; mean trust>4
Implementation—retention	Proportion completing the T1 survey after completing the chatbot pathway	T1	70% or more of the participants completing a session
Maintenance	Tool uptime (percentage of time that the chatbot is accessible) and reported error or failure rates	After T1	≥80% uptime and ≤20% error or failure rate

a DSES: Decision Self-Efficacy Scale.

b GHSQ: General Help Seeking Questionnaire.

c T0: baseline.

d T1: after interaction with the chatbot.

e BUS-11: Bot Usability Scale.

f AIM: Acceptability of Intervention Measure.

g IAM: Intervention Appropriateness Measure.

h TPA: Trust Between People and Automation scale.

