#### Proposed Approach

We propose a nonrandomized feasibility pilot that deploys the community-informed SARHAchat prototype on 2 social media platforms identified by the target population (ages of 18‐25 years; HRSA-designated rural NC and SC counties) during phases 1 and 2. This “meet people where they are” implementation strategy departs from traditional clinic-based digital health delivery and tests a potentially more equitable and scalable approach to reaching rural young adults.

A total of 75 pregnancy-capable individuals aged 18 to 25 years residing in HRSA-designated rural counties will be recruited via social media geofencing, accounting for a projected 20% attrition rate and yielding a target of 60 completers, which is consistent with published recommendations for digital health feasibility studies [27]. To achieve this within a 16-week recruitment window, the required enrollment rate is approximately 4.7 participants per week. Prospective monitoring will trigger adaptive recruitment if fewer than 30 participants have been enrolled by week 8.

Eligible participants will complete an electronic informed consent form and a baseline survey (T0; digital health literacy, decision self-efficacy, and demographics), immediately engage with the enhanced SARHAchat prototype to complete one pathway (eg, contraception consultation or question-and-answer session) with a guided prompt or their own questions, and then complete a postinteraction survey (T1; usability, acceptability, appropriateness, trust, and decision self-efficacy). A purposively selected subsample of 20 participants will complete semistructured interviews to provide explanatory qualitative depth (Figure 2).

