### Progression Criteria

The prespecified criteria for advancing to an effectiveness trial are as follows: reach of 60% or more; retention of 70% or more; mean Bot Usability Scale, Acceptability of Intervention Measure, and Intervention Appropriateness Measure scores above 4; mean distrust score below 4; mean trust score above 4; and 70% or more of the participants completing the chat session and T1. Effectiveness measures (DSES and GHSQ) are exploratory, intended to inform the design of any future effectiveness trial, and are not progression metrics. If the criteria are not met, qualitative findings will be used to determine whether barriers are modifiable at the design level or structural, distinguishing between tool adaptation and revision of the implementation strategy as the appropriate response.

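### The appropriateness (IAM) progression cut-off is a mean above 3 in Table 1 but above 4 in Progression Criteria, so a mean above 3 and up to 4 both passes and fails

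*Protocol article*

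**What the plan says.** Table 1 of the protocol article (Data Analytical Plan, Phase 3) is captioned as giving "prespecified progression thresholds for aim 2". Its row for appropriateness and trust, measured at T1, reads "Mean IAM>3; mean distrust<4; mean trust>4". A table footnote expands the abbreviation: "IAM: Intervention Appropriateness Measure". The Phase 3 analysis text cites this table as the set of progression thresholds against which the feasibility outcomes will be set.

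The Progression Criteria section then opens with "The prespecified criteria for advancing to an effectiveness trial are as follows" and includes in its list "mean Bot Usability Scale, Acceptability of Intervention Measure, and Intervention Appropriateness Measure scores above 4". That section also says that, if the criteria are not met, qualitative findings will be used to judge whether the barriers lie in the design or are structural.

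**The concern.** Both places claim to hold the prespecified rule, and they give different numbers for the same measure. A reader cannot tell from the article whether an IAM mean of, say, 3.5 counts as a success.

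This matters because IAM is one of the named conditions for moving to an effectiveness trial, and the article describes feasibility evidence as its primary contribution. Progression criteria are useful because they are fixed before results are known. With two published cut-offs, the team could report against either one after seeing the data and cite the article in support. The IAM criterion would then no longer be prespecified in any real sense. The joint display that feeds the progression decision would also carry an ambiguous verdict for this measure.

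**Working it through.** **1. Are the two statements about the same thing?** The Table 1 footnote identifies IAM as the Intervention Appropriateness Measure, which is the instrument named in Progression Criteria. Both rules use the mean score from the phase 3 pilot. The Table 1 caption refers to aim 2, whereas the pilot is the third objective in the abstract. The table nevertheless lists the phase 3 measures at T0 and T1 and is cited from the Phase 3 analysis text, so that label does not separate the two rules.

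**2. Do the other scale means agree?**

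| Measure | Table 1 | Progression Criteria | Agree? |
|---|---|---|---|
| BUS-11 | mean >4 | mean above 4 | yes |
| AIM | mean >4 | mean above 4 | yes |
| IAM | mean >3 | mean above 4 | **no** |
| Distrust | mean <4 | mean below 4 | yes |
| Trust | mean >4 | mean above 4 | yes |

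Among the scale means, only IAM differs.

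**3. Which results are affected?** Apply both rules to an observed mean m:

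| Observed mean | Table 1 (m>3) | Progression Criteria (m>4) |
|---|---|---|
| 3.0 or lower | fail | fail |
| 3.01, 3.5, 3.9, 4.0 | pass | fail |
| 4.01, 4.5 | pass | pass |

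Both inequalities are strict, so the conflict covers 3 < m ≤ 4, including exactly 4. This step needs no assumption.

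**4. How likely is a conflicting verdict?** The documents give no expected IAM mean or SD, so this step is illustrative. The one input from the article is the number of completers: "accounting for a projected 20% attrition rate and yielding a target of 60 completers", that is 75 × (1 − 0.20) = 60, which reproduces the stated target. With a normal approximation, SE = SD/√n and P(mean > c) = 1 − Φ((c − μ)/SE).

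Assume μ = 3.7 and n = 60:

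| SD | SE | (4 − 3.7)/SE | P(mean >4) | P(mean >3) |
|---|---|---|---|---|
| 0.6 | 0.077 | 3.87 | 0.00005 | about 1 |
| 0.8 | 0.103 | 2.90 | 0.0018 | about 1 |
| 1.0 | 0.129 | 2.32 | 0.010 | about 1 |

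Varying the assumed true mean, with SD 0.7 to 1.0 and n from 45 (the Reach threshold for enrollment) to 60 (the completer target), the probability that the two rules disagree, P(mean >3) − P(mean >4), is:

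| True mean | Probability of opposite verdicts |
|---|---|
| 3.25 or 3.75 | 0.95 to 0.997 |
| 3.5 | about 0.999 or more |
| 4.0 | 0.50 |
| 4.25 | 0.003 to 0.05 |

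**The case against.** The strongest reply is that only the Progression Criteria section states the rule for advancing, and that Table 1 is a reporting frame organized by RE-AIM domain. In support, Table 1 has a Maintenance threshold that the Progression Criteria list does not carry over. On that reading an IAM mean above 3 and up to 4 simply fails. The reading is weak, however: the table's own caption calls its values progression thresholds, the Phase 3 analysis text does the same, and no sentence gives one place precedence.

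A second reply is that little hangs on it. The pilot is nonrandomized and descriptive ("we will perform descriptive analyses to present participants’ characteristics"). IAM is one criterion among several, and a missed criterion leads to qualitative review rather than automatic termination. The conflict changes the overall verdict only if IAM falls in the disputed interval and every other criterion is met. That condition is real and limits the consequence. It does not make the criterion usable as written.

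A third reply is that the probability example uses a true mean chosen inside the disputed interval. That is fair. The documents do not say where the mean is expected to fall, and the calculation above shows the conflict almost vanishing at a true mean of 4.25. The example shows what could happen; it is not a forecast.

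Finally, the match with the AIM and BUS-11 cut-offs may hint that the table entry is the slip. It is no more than a hint: the article gives no response range for these scales, so equal cut-offs need not be equally demanding.

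**Conclusion.** The contradiction holds. It is in the current text, both values are legible, and it concerns a threshold on which the decision to advance depends. Every observed IAM mean above 3 and up to and including 4 receives opposite verdicts; this follows from the two statements alone. How often it would happen depends on assumed values: it is near certain for true means around 3.25 to 3.75, an even chance at 4.0, and unlikely at 4.25. The documents do not show which cut-off was intended. This is not a detail that an article may leave to a fuller document, because the article states the number twice, with two values. It should be settled before pilot data exist.

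**What to change.** Choose one IAM cut-off, give a short reason for it, and state it identically in Table 1 and in Progression Criteria.

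- If above 4 is intended, change the IAM entry in Table 1. IAM then has the same numerical cut-off as AIM and BUS-11, and the criterion is harder to meet than the table now suggests.
- If above 3 is intended, take IAM out of the group of measures required to exceed 4 in Progression Criteria, give it its own clause, and say why appropriateness has a lower bar than acceptability and usability.
- If a minimum and a target were meant, label them as such and say which one governs progression.

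The cost is one table cell or one sentence, with no change to sample size, measures or procedures. Phase 3 recruitment is projected for January 2027, so the correction can be dated and recorded before any pilot result is seen.

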### Data Integrity, Missing Data, and Handling of Incomplete or Failed Interactions

A participant is classified as a completer only when the Qualtrics (Qualtrics International Inc) T0 submission, the back-end pathway-complete event, and the Qualtrics T1 submission all exist for the same study ID (Figure 2). All thresholds are calculated against the number enrolled except for retention, which is calculated among pathway completers to isolate postengagement attrition. Geographic eligibility will be verified by comparing self-reported county with the IP address captured by the Qualtrics screener; discordant or anonymized (eg, virtual private network) locations will be manually reviewed and screened out if unresolved via a brief verification contact. Duplicate enrollment and potential bot submissions will be addressed through Qualtrics duplicate submission and bot controls. Only the first consented record will be retained. IP addresses will remain in the siloed screening dataset, used solely for eligibility verification and duplicate detection, and will be deleted when recruitment closes.

Participants without a pathway-complete event within 2 days of T0 will be counted as noncompleters for the adoption threshold, and their partial engagement (number of exchanges and last conversational stage reached) will be described to identify points of disengagement. Back-end logs will distinguish verified technical failures (system unavailability, response generation errors, and loss of session state) from user abandonment and from safety guardrail activations, which reflect intended behavior and are reported separately. Technical failures contribute to the maintenance error rate (≤20%), and affected participants may reattempt using their original study ID, with adoption status determined via eventual pathway completion. Participants whose session is interrupted by a technical failure may resume via their original study ID within 7 days; sessions not completed within this window are classified as noncompleters. Given the pilot’s descriptive scope, analyses will follow an available-case approach. Scale scores will be computed when at least 80% of items are answered, DSES change will be limited to participants who complete both T0 and T1, and baseline characteristics of completers and noncompleters will be compared descriptively.

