Participants will access SARHAchat through a study URL and a unique study ID. Before engaging with the chatbot, participants must acknowledge a safety statement explaining that the chatbot provides informational support only and is not a substitute for clinical care and that they should consult a health care professional for evaluation, diagnosis, or treatment as needed (Figure 1). Participants will be instructed not to enter names, addresses, phone numbers, exact locations, names of partners or family members, or other directly identifying information into the chatbot. To further reduce unnecessary disclosure, phase 3 will offer 2 modes of engagement: guided prompts that allow participants to explore common SRH topics without typing personal questions and optional free-text entry for participants who wish to ask their own questions. High-risk prompts, including those involving urgent symptoms, sexual coercion, partner violence, or emotional crises, will trigger predefined safety and referral responses directing users to emergency, clinical, or crisis services as appropriate.

Participants will be compensated for their time in recognition of their contribution to the study. Compensation is structured by study phase: US $50 for phase 1 interviews, US $100 for phase 2 feedback session participation, and US $45 for phase 3 chatbot interaction and T1 survey completion, with an additional US $50 for those who choose to participate in a follow-up phase 3 interview.

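### Five of the eight progression criteria are means of T1-only scales, so they cannot use the enrolled denominator the plan states, and a narrow pass may not hold for everyone enrolled

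*Protocol article*

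**What the plan says.** Under Data Integrity, Missing Data, and Handling of Incomplete or Failed Interactions, the protocol article gives one denominator rule: "All thresholds are calculated against the number enrolled except for retention". Retention is taken among pathway completers. The same section says that "analyses will follow an available-case approach" and that a scale is scored when at least 80% of its items are answered. It gives no imputation or bounding rule for people without T1 data.

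The phase 3 Proposed Approach and Table 1 place BUS-11, AIM, IAM and the trust and distrust scores at T1 only, after the chatbot interaction. The sample size is set "accounting for a projected 20% attrition rate and yielding a target of 60 completers".

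Progression Criteria lists eight conditions: reach; retention; the BUS-11, AIM and IAM means; "mean distrust score below 4; mean trust score above 4"; and at least 70% completing both the chat session and T1. Five of the eight are scale means.

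**The concern.** A mean of a scale that exists only at T1, analysed on available cases, has T1 respondents as its base. It cannot also be calculated against the number enrolled. As written, a reader of the results could take a usability or trust pass to describe everyone enrolled when it describes those who stayed.

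Staying may be related to what is rated. The Introduction and the phase 2 rationale argue that poor fit leads to low engagement, and low usability or trust is a natural reason to leave. The described sequence puts T1 after the pathway, and the stated payment is "US $45 for phase 3 chatbot interaction and T1 survey completion", so the article describes no route by which someone who abandons the chat would rate it. If leavers would have scored the tool lower, the observed means are too favourable: too high for usability, acceptability, appropriateness and trust, and too low for distrust. These means are go/no-go conditions for an effectiveness trial, so a result just past the bar could depend on who answered.

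**Working it through.** **Inputs from the article.** 75 enrolled, 20% attrition and 60 completers (phase 3 Proposed Approach). Bars of above 4 for BUS-11, AIM, IAM and trust, and below 4 for distrust (Progression Criteria). At least 70% completing chat and T1 (same section).

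**Assumptions.** The article gives no scale ranges or standard deviations. A 1 to 5 scale, the observed means and the nonrespondent means below are illustrative. The break-even formula does not depend on the scale range; the range only decides which nonrespondent means are attainable.

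**The plan's own figures reproduce.** 60 / (1 − 0.20) = 75, and 75 × 0.80 = 60. Reach: 0.60 × 75 = 45.

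**How much nonresponse a passing pilot can have.**
- Planned: 75 − 60 = 15 of 75, or 20%.
- At the joint completion floor, with the enrolled as denominator: 0.70 × 75 = 52.5, so at least 53 are needed. That leaves 22 of 75, or 29.3%.

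**Mean over all enrolled.** With p the share who have T1 scores, y the observed mean and m the nonrespondent mean:

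enrolled mean = p·y + (1 − p)·m, and the overstatement is (1 − p)·(y − m).

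- y = 4.2, m = 3.0, p = 0.80: 3.36 + 0.60 = 3.96.
- y = 4.2, m = 3.0, p = 53/75: 2.968 + 0.880 = 3.85.
- For a 1-point gap the overstatement is 0.20 at p = 0.80 and 0.29 at p = 53/75.

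**Break-even.** The criterion fails over all enrolled when m is at or below (4 − p·y) / (1 − p).

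| Observed mean | p = 0.80 | p = 53/75 |
|---|---|---|
| 4.1 | 3.60 | 3.76 |
| 4.2 | 3.20 | 3.52 |
| 4.3 | 2.80 | 3.28 |
| 4.5 | 2.00 | 2.80 |

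For distrust the direction flips. An observed 3.8 fails over all enrolled if nonrespondents average 4.80 or more (p = 0.80) or 4.48 or more (p = 53/75).

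**Two qualifications on p.** The joint criterion counts T1 submissions, not scored scales, so the 80%-of-items rule can lower p a little for a given scale. Conversely, a T1 return without a pathway-complete event would raise it.

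**The case against.** The strongest reply is that leavers are not ignored. They count as failures in adoption, which is taken over all enrolled, and in the 70% chat-plus-T1 criterion. Heavy abandonment therefore gives a no-go whatever the means say. This stands, and it limits the problem to the scale-mean components and to roughly 20% to 29% nonresponse. A reader might multiply Table 1's separate adoption and retention floors (0.70 × 0.70 = 49%) and infer that a go could rest on half the sample. With the enrolled as its denominator, the joint criterion in Progression Criteria rules that out.

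A reader might also infer that a pass is biased upward as a matter of fact. The documents do not show this. People may leave for reasons unrelated to usability or trust, and the plan separates technical failures from abandonment and lets affected participants resume. Nor does the text restrict the scale means to completers. It defines a completer as someone for whom the T0 submission, "the back-end pathway-complete event, and the Qualtrics T1 submission all exist for the same study ID", but does not apply that definition to the T1 scores. The flow figure is not available to settle this.

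There are other safeguards. Partial engagement is described, baseline characteristics of completers and noncompleters are compared, and the 20 interviews are sampled across engagement levels and feed the progression decision. They help interpretation but do not change what a numeric threshold is measured on. Available-case means are ordinary in a descriptive pilot. The difficulty is that the text claims a different denominator for means that serve as go/no-go conditions.

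**Conclusion.** The concern holds in a limited form. The denominator sentence cannot be true for BUS-11, AIM, IAM, trust and distrust, which make up five of the eight progression criteria. It is also inexact for reach, which Table 1 sets against the target. Favourable bias in the five means is possible, not demonstrated.

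On the stated assumptions the possible overstatement is about 0.2 to 0.3 points for a 1-point gap between respondents and nonrespondents. That can reverse a narrow pass such as 4.1 or 4.2. A clear pass such as 4.5 would reverse only if nonrespondents averaged about 2.0 (80% response) or 2.8 (53 of 75).

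The documents do not support the wider reading that the progression rule as a whole would pass a tool that people abandon, and nothing here requires a change to how T1 is distributed or paid for. The point should be settled before phase 3 recruitment, projected for January 2027, because it changes what a narrow pass may be said to show.

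**What to change.** - **Correct the denominator sentence.** Adoption and the joint chat-plus-T1 criterion use the number enrolled; retention uses pathway completers; reach uses the target of 75; scale means use T1 respondents with a scored scale, shown with their number and percentage of those enrolled.
- **Add a break-even value beside each scale mean**, namely the nonrespondent mean at which the criterion would fail over all enrolled: (bar − p·y) / (1 − p). Describe a pass as applying to T1 respondents, and as sensitive to nonresponse when the break-even value is close to the observed mean. The study team should fix beforehand what counts as close.
- **Reconcile the IAM bar first.** It is above 3 in Table 1 and above 4 in Progression Criteria, and the break-even needs a single value.

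The cost is a reworded sentence, one small table and a slightly more cautious statement of a narrow pass. Data collection does not change.
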